### Arithmetic task

The arithmetic task will consist of two-digit addition and subtraction problems with two operands resulting in a two-digit solution [https://osf.io/6emdy/]. The carry and borrow operations will be manipulated categorically, i.e., addition problems with and without carrying (e.g., 51 + 43 vs. 58 + 36) as well as subtraction problems with and without borrowing (e.g., 94–43 vs. 94–36), and continuously, i.e., unit sum in addition (e.g., 14 in 58 + 36) and unit difference in subtraction (e.g.,– 2 in 94–36).

The stimulus set consists of 128 arithmetic problems with 32 trials per condition, i.e., addition with/without carrying and subtraction with/without borrowing. The stimulus generation will consider unit sum in addition and unit difference in subtraction to be relatively equally distributed. This means that addition problems (*a* + *b* = *r*) cannot be directly transformed by inversion into subtraction problems (*r*–*b* = *a*). Nevertheless, the numerical properties will be matched across conditions: *a* and *b* will be closely matched in their numerical magnitude and parity; the position of the larger operand will be counterbalanced; pure decades as well as ties within and between *a*, *b*, and *r* will be excluded [25, 42, for decades see 48, for ties see 49].

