The task will be computerized in the program OpenSesame [50]. Each arithmetic problem will be presented centered in white against a black background. In an oral production paradigm, the subjects will be asked to mentally solve the problem as quickly and accurately as possible and to respond while pressing the space bar. Button press and button release will be recorded and the experimenter will blindly note the given responses. Each stimulus will be presented with a time limit of 30 s and disappear upon button press to emphasize mental arithmetic before responding. In the inter-trial interval, a black screen will be shown with a duration of 4–7 s (jittered in steps of 0.5 s, mean of 5.5 s), including a white fixation point in the last 0.5 s. The 128 trials will be presented in 4 runs of 32 trials each (8 trials per condition) and the trial order will be pseudorandomized for every subject with no more than two trials of the same condition presented consecutively. As dependent variables, error rates (ER) are defined as the number of incorrectly solved and time-out trials divided by the total number of completed trials, and reaction times (RT) as the duration between stimulus onset and button press.

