### Data analysis

#### Data exclusion for subjects

Subjects will be excluded from all analysis when the inclusion criteria are not met (regarding age, handedness, language, health, and, for elderly subjects, cognition), when more than 50% of the behavioral data of the arithmetic task is missing (due to drop out or experimental or technical problems), or when the error rate in the arithmetic task is larger than 50% (because of the exclusion of incorrectly solved trials). Moreover, an outlier analysis will be conducted specific to the respective age group to exclude subjects deviating more than 3 median absolute deviations from the group’s median in RT of the arithmetic task from all analysis [58]. Subjects will be excluded only from neural data analysis in case of more than 50% missing neural data of the arithmetic task (due to drop out, experimental or technical problems, trial exclusion and artifact rejection), or in case of more than 3 noisy channels (restricting channel interpolation to a maximum of 3 channels). Furthermore, a case-wise exclusion of subjects from the respective analysis of the demographic variables (age, gender, education) or control measures (processing speed, working memory, and verbal and non-verbal intelligence) applies in case of missing or incomplete data, or an ACC below 33% in the working memory task.

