#### Data exclusion for trials

Trials will be excluded from the RT analysis (arithmetic and working memory task) as well as from the fNIRS analysis (arithmetic task) when the trial was not correctly solved, when the RT was below 200 ms (anticipations), when the RT deviates more than 3 median absolute deviations from the subject’s median in the respective task, and when the duration between button press and button release deviates more than 3 median absolute deviations from the subject’s median in the arithmetic task [58].

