Prior to the analyses of the arithmetic task, cognitive abilities will be analyzed: children and the elderly will be compared to young adults regarding processing speed (raw scores), working memory (ACC), and verbal and non-verbal intelligence (IQ scores) by two-sided Bayesian independent samples *t*-tests. Next, the arithmetic task will be analyzed in 3 age (children, adults, elderly) × 2 operation (addition, subtraction) × 2 complexity (with, without carry/borrow) Bayesian repeated measures ANOVAs [analysis over subjects, averaged over trials]. For effects with *BF*_*10*_ or *BF*_*01*_ ≥ 6, post-hoc two-sided tests will be conducted for the contrast children vs. young adults and the contrast young adults vs. the elderly by means of Bayesian independent samples *t*-tests, or for contrasting different conditions by means of Bayesian paired *t*-tests. Finally, multi-model Bayesian regressions will be conducted with the categorical predictor carry/borrow (with, without) and the continuous predictor unit sum/difference separately for addition and subtraction and for every age group [analysis over trials, averaged over subjects]. All confirmatory analyses will be conducted on the dependent variables RT, indicating behavioral performance, and beta values, indicating neural activation for each ROI separately (left/right IFG, MFG, IPS). Planned exploratory analyses will be conducted on ER and beta values for neural activation in the other ROIs (left/right AG, SMG).

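### The H3 regressions use problem means that each rest on a different set of subjects, with no subject term; this adds noise and can flatten the slopes, most in the age group with most errors

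*Protocol article*

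**What the plan says.** For H3, the Statistical data analysis section states that "multi-model Bayesian regressions will be conducted with the categorical predictor carry/borrow (with, without) and the continuous predictor unit sum/difference". No other predictor is named. Each operation has its own regression within each group, and the data points are problems, not persons: "for every age group [analysis over trials, averaged over subjects"]. In the Arithmetic task section, "The stimulus set consists of 128 arithmetic problems with 32 trials per condition", so each regression has 32 + 32 = 64 problem means.

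Three other rules decide which responses enter a problem mean:

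- Data exclusion for trials removes a trial from both the RT and the fNIRS analysis "when the trial was not correctly solved, when the RT was below 200 ms (anticipations"), or when its RT or button-press duration lies more than 3 median absolute deviations (MAD) from that subject's median.
- The Arithmetic task section says that "error rates (ER) are defined as the number of incorrectly solved and time-out trials divided by the total number of completed trials", so a trial that reaches the 30 s limit counts as an error.
- Data exclusion for subjects drops a subject for errors only "when the error rate in the arithmetic task is larger than 50% (because of the exclusion of incorrectly solved trials"). A retained subject can therefore lack up to half of the problems.

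RT and beta values are confirmatory; error rate is exploratory. The Bayes factor design analysis lists both H3 effects, in each age group, among the effects that must reach a Bayes factor of 6 before sampling can stop early.

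**The concern.** A regression over problem means assumes that the means differ because the problems differ. Here they also differ because the contributing subjects differ. A problem that many weaker subjects fail is averaged over the remaining, stronger ones. Subjects vary in overall speed, and nothing in the stated model takes that variation out.

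Two consequences need to be kept apart. The first is noise: the changing mix of fast and slow subjects moves the problem means even when accuracy and speed are unrelated. The second is bias: if subjects who fail hard problems are also slow, hard problems look faster than they are and the slope is flattened.

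Both grow with the error rate. H3 compares age groups on which of the two effects is present, and the plan expects children and the elderly to perform worse than young adults. A group with more errors can miss the threshold for an effect it has as strongly as the others. Because the H3 effects also feed the stopping rule, weakened evidence makes sampling to the maximum of 60 per group more likely.

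**Working it through.** **1. The plan's own figure.** The design analysis gives a 61% chance of detecting δ = 0.5 before the maximum sample. Simulating the two-sample, two-sided Bayesian t-test (Cauchy scale 0.707, tested after each added subject per group from 20 to 60, threshold 6, 20,000 runs) gives 59.7% before n = 60 and 60.7% through n = 60. The figure reproduces, but it describes a two-group t-test and says nothing about the H3 regressions.

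**2. Noise, by formula.** Let S be the between-subject SD of RT, σ the trial SD, p the share of trials lost and m = 60(1 − p) the subjects left per problem. If losses fall at random across subjects, the changing mix adds variance S²p/m to each problem mean, against trial variance σ²/m. The ratio is (S/σ)²p.

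Assumed inputs: RT 7 s, subject log-SD 0.4, trial log-SD 0.3, so roughly S = 7 × 0.4 = 2.8 s, σ = 7 × 0.3 = 2.1 s and (S/σ)² = 1.78.

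| p | m | SD from changing mix | SD from trial noise | Variance ratio |
|---|---|---|---|---|
| 4% | 57.6 | 2.8√(0.04/57.6) = 0.07 s | 2.1/√57.6 = 0.28 s | 0.07 |
| 18% | 49.2 | 2.8√(0.18/49.2) = 0.17 s | 2.1/√49.2 = 0.30 s | 0.32 |
| 24% | 45.6 | 2.8√(0.24/45.6) = 0.20 s | 2.1/√45.6 = 0.31 s | 0.43 |

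A subject term removes the third column. No link between accuracy and speed is needed for it to arise.

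**3. Bias, by formula.** Let sᵢ be subject i's speed level and eᵢ the chance that this subject fails a given problem. The expected speed level of those who remain is s̄ − Cov(s, e)/(1 − p). If slow subjects fail more often, the covariance is positive and the mean drops, by more on problems with more errors. The bias falls on the predictor along which errors rise. If accuracy and speed are unrelated, the covariance is zero.

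**4. Size, by simulation.** The documents give no error rates by group or problem and no accuracy-speed correlation, so these inputs are assumed. Setting: 64 addition problems, unit sums 2-9 without and 10-17 with carry; subjects above 50% errors dropped; errors and RTs beyond 3 MAD removed; Jeffreys-Zellner-Siow (JZS) prior r = 0.354; inclusion Bayes factors; 60 subjects; a real effect of both kinds in every group.

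Slope from correct-only problem means relative to all trials, accuracy-speed correlation 0.3-0.7:

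- Children, errors rising steeply with unit sum: continuous 0.74-0.89, categorical 0.87-0.94.
- Children, errors rising with carry only: continuous 1.00-1.01, categorical 0.80-0.91.
- Young adults (7% errors): 0.96-0.98 for both. Elderly (8% errors): 0.94-0.98 for both.

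The 3-MAD trim takes a further 5-9% or so in every group.

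Chance of an inclusion Bayes factor of at least 6 at correlations 0.3 / 0.5 / 0.7:

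| Group and error pattern | Effect | All trials | Plan | Subject-adjusted |
|---|---|---|---|---|
| Children, steep with unit sum (25% errors) | continuous | 0.81 / 0.80 / 0.79 | 0.51 / 0.45 / 0.37 | 0.75 / 0.76 / 0.75 |
| | categorical | 0.92 / 0.91 / 0.90 | 0.76 / 0.70 / 0.66 | 0.90 / 0.84 / 0.88 |
| Children, carry only (20% errors) | continuous | 0.87 / 0.80 / 0.84 | 0.79 / 0.76 / 0.75 | 0.84 / 0.82 / 0.80 |
| | categorical | 0.89 / 0.91 / 0.88 | 0.69 / 0.69 / 0.56 | 0.87 / 0.89 / 0.86 |
| Young adults (7% errors) | continuous | 0.87 / 0.84 / 0.84 | 0.84 / 0.77 / 0.78 | 0.88 / 0.86 / 0.85 |

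The plan and adjusted columns use the same retained trials, so the gap between them is the effect of the subject term alone. Evidence for no continuous effect in children (BF01 of at least 6) appeared in 0-6% of runs.

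A further set at about 18% errors, covering correlations of 0 and −0.3 and carry-only errors as well, gave 0.84-0.91 (all trials), 0.37-0.78 (plan) and 0.79-0.85 (adjusted) for the continuous effect. Adjustment helped in every setting, and BF01 of at least 6 stayed at or below 9%.

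**The case against.** A reader might infer more: that the averaging hides the continuous effect in children and so manufactures the pattern H3 predicts. The documents do not support that, for four reasons.

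- **Direction.** The Introduction ties higher error rates to problems with versus without carry or borrow, not to unit sum, and describes children's effects as categorical. If children's errors step at carry, the selection bias falls on the categorical slope, which H3 expects to see in children.
- **Decision rule.** Support for absence needs BF01 of at least 6, which is rare here. Missing the threshold for presence is inconclusive and confirms nothing.
- **The elderly.** They too are expected to perform worse than young adults. Flattening their continuous slope works against H3.
- **Correlation.** A positive accuracy-speed link is assumed. Subjects are told to be both fast and accurate, so a trade-off is possible; at a correlation of −0.3 one check gave a continuous slope ratio of 1.02, that is, no flattening.

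It can also be said that 50% is a ceiling and not an expected error rate, that subjects with outlying RT are removed within each age group, and that the exploratory error-rate analyses could show group differences. Continuous difficulty is itself uncertain for subtraction, according to the Introduction.

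These points limit the direction and size of the bias, but they leave the noise mechanism standing. With errors tied to carry only, about 20% errors and a large assumed carry effect (2.5 s), the continuous effect was detected in 0.87-0.88 of runs with complete data, 0.66 under the plan and 0.77 after adjustment, at correlations of 0, 0.3 and 0.7 alike. Carry was detected in every run. Unequal detection across groups can therefore arise without selection bias, through lost precision. The error-rate analyses may reveal the problem but do not correct the regressions.

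**Conclusion.** The point holds in a limited form. As written, the H3 problem means rest on differing sets of subjects and no term removes subject differences. This costs precision whatever the accuracy-speed correlation. It biases slopes toward zero only if accurate subjects are also faster, and which slope suffers depends on where errors rise. The group with most errors loses most; that may be children, and possibly the elderly. The practical harm is that a difference in accuracy between age groups may be read as a difference in processing. It does not by itself confirm H3.

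All sizes rest on assumed error rates, RTs, effect sizes and correlations, and were worked out only for RT in addition. None is available for subtraction or for beta values, although the same trial exclusion and averaging are planned for both.

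**What to change.** Replace the averaging step. For each age group and operation, fit RT = subject + problem to the retained correct trials, then regress the 64 subject-adjusted problem effects on carry/borrow and unit sum/difference with the priors already planned. Alternatively, fit one trial-level model with subject intercepts and these predictors, keeping a problem term so that problems remain the unit of replication. It would also help to report, by age group, how many subjects contribute to each problem.

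The cost is one extra modelling step on data already held, with no added testing. The adjustment does not undo the shortening caused by the 30 s limit or the 3-MAD trim, so some flattening of the slopes will remain.

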### Bayes factor design analysis

For sample size estimation, the sequential Bayes factor design with maximal *n* will be used [65, 66]. In this design, data collection (1) will start with a minimum sample size of *n*_*min*_ = 20 per group, (2) will continue until a *BF*_*10*_ or *BF*_*01*_ ≥ 6 is obtained for all effects of interest, or (3) will be stopped when a maximum sample size of *n*_*max*_ = 60 per group has been reached. The properties of the planned research design were estimated with Monte Carlo simulations according to Schönbrodt and Wagenmakers [65]: The minimum sample size was set for reducing false positive rates, and the maximum sample size was set to ensure feasibility, while 80% of studies with an infinite sequential sampling stop earlier than *n*_*max*_. If sampling is terminated because of reaching *n*_*max*_, only with a probability of 5% will the study obtain misleading evidence. This design detects an expected medium effect size of *δ* = 0.5 with a probability of 61% before the *n*_*max*_ is reached. The chosen medium effect size accounts for the bias of small samples in the reported large effect sizes ($\eta_{p}^{2}$ ≈ .5) for differences between children, young adults, and the elderly in the neural distance effect [67, for large effect sizes (*d* ≈ 1.2–1.6) see also for children vs. adults: 68, for younger adults vs. the elderly: 69].

The effects of interest according to the hypotheses include the main effect of age (ANOVAs) for RT and activation in left IFG, bilateral MFG, and left IPS according to H1; the main effect of complexity and the interaction effect of complexity and age (ANOVAs) for RT and activation in left IFG and bilateral MFG according to H2; the categorical carry/borrow effect and the continuous effect of unit sum/difference in each age group (regressions) in RT and neural activation in left IPS according to H3.

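### The 61%, 80% and 5% design figures describe a single effect, but the stopping rule requires BF ≥ 6 for all 37 effects of interest, and the simulated test is not named

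*Protocol article*

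**What the plan says.** The protocol article, under Bayes factor design analysis, sets a sequential design with a minimum of 20 and a maximum of 60 per group. Sampling goes on until a Bayes factor of at least 6 in either direction "is obtained for all effects of interest, or (3) will be stopped when a maximum sample size of" 60 per group is reached.

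The same section defines the set, beginning with "The effects of interest according to the hypotheses include the main effect of age (ANOVAs) for RT and activation in left IFG". For H1 the age effect is also listed for MFG on both sides and for left IPS. H2 adds complexity and complexity × age for RT, left IFG and MFG on both sides. H3 adds the categorical and continuous effects in each age group for RT and left IPS. The Statistical data analysis section adds that each ROI is analysed separately, and that the regressions are run separately for each operation and age group, over trials averaged over subjects.

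The design's performance is introduced by "The properties of the planned research design were estimated with Monte Carlo simulations", with a cited method paper. Three figures are given:
- on detection: "This design detects an expected medium effect size of *δ* = 0.5 with a probability of 61% before the *n*_*max*_ is reached";
- on early stopping: "while 80% of studies with an infinite sequential sampling stop earlier than *n*_*max";
- on studies that end at the maximum: "only with a probability of 5% will the study obtain misleading evidence".

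Only one effect size is given. The simulated test is not named, and there is no joint probability over the listed effects.

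**The concern.** An operating characteristic belongs to a stopping rule. Here the rule is a conjunction over many effects, while the figures are for one effect. A reader will take 61% and 80% as the chance of a decisive result and of an early stop in this study. Under the rule as written both are likely to be much lower, so the expected sample size, the recruitment forecast and the stated efficiency of sequential sampling would all be misjudged. The 5% has a related problem: it covers only studies that reach the maximum, so it says nothing about wrong decisions made by crossing a boundary earlier.

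**Working it through.** **1. Count of effects.** Left and right MFG count separately because each ROI is analysed separately.
- H1: age on RT, left IFG, left MFG, right MFG, left IPS = 5.
- H2: 2 effects × 4 variables (RT, left IFG, left MFG, right MFG) = 8.
- H3: 2 predictors × 3 age groups × 2 operations × 2 variables (RT, left IPS) = 24.
- Total: 5 + 8 + 24 = 37.

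**2. Can the stated figures be reproduced?** Inputs from the article: boundary 6, n from 20 to 60 per group, δ = 0.5, Cauchy scale 0.707 for t-tests and 0.5 for ANOVA fixed effects. Assumption: a look after every added subject per group. The Bayes factors are the JZS type, evaluated by Monte Carlo. The ANOVA column is one between-subject age effect with one group shifted by 0.5 SD.

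| Quantity | Article | One two-sided two-group t-test | One three-group ANOVA effect |
|---|---|---|---|
| Reaches BF10 ≥ 6 by n = 60 | 61% | 61% | 61% |
| Stops before n = 60 | 80% | 60% | 80–81% |
| Crosses BF01 ≥ 6 first (wrong) | not given | 0% | about 20% |
| BF01 > 3 at n = 60, among studies reaching it | 5% | 12.6–12.9% | about 7% |
| The same, as a share of all studies | – | 5.0% | 1.3% |

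The fourth row takes misleading evidence to mean BF01 > 3, which is an assumption; the article does not define it.

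In the t-test the largest possible BF01 (at t = 0) is 5.14 at n = 60. It first exceeds 6 at n = 85 (5.99 at 84, 6.03 at 85), so the H0 boundary cannot be crossed within the design. With open-ended sampling, 80% of t-test studies have stopped only by n = 89. In the three-group ANOVA the largest BF01 is already 7.4 at n = 20 and 17.7 at n = 60, so that boundary is reachable throughout. Neither model gives all three figures as worded, and each figure that is matched is matched by one effect.

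**3. The all-effects rule.** Assumptions: every effect has δ = 0.5, a t-test stands in for each effect, and the correlation ρ is equal between all effects. The article gives no correlations, so a range is shown. In each range the lower value requires all effects at the same look, the upper requires each effect at some look. The independence bound is 0.61^k: 0.61^5 = 8.4%, 0.61^13 = 0.16%, 0.61^37 = 1.1 × 10⁻⁸.

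| Effects that must all reach BF ≥ 6 by n = 60 | ρ = 0 | ρ = 0.5 | ρ = 0.8 |
|---|---|---|---|
| 5 (H1 only) | 4–9% | 23–26% | 37–40% |
| 13 (H1 and H2) | 0–0.2% | 10–13% | 27–30% |
| 37 (all) | about 0% | 3–5% | 20–22% |

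**4. The H3 terms.** Each regression has 2 × 32 = 64 items. With the planned prior (0.354), the largest inclusion BF01 at 64 items is about 3.6 when neither predictor explains variance. It passes 6 only when the other predictor explains about half the variance. H3 itself expects rather categorical effects in children and rather continuous ones in the elderly, so some of these terms are expected to be weak. Extra participants add no items; they only make the item means less noisy.

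**The case against.** Three stronger readings are tempting, and the documents do not support them.

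A reader might infer that the figures come from a two-group t-test. The article never says so, and the 80% speaks against it; a single ANOVA effect fits 61% and 80% better. The origin must stay open.

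A reader might infer that early stopping has essentially no chance. That needs near-independence. The effects share subjects and the ROIs are probably correlated; at ρ = 0.8 about one study in five would meet the rule. The Introduction describes well-established behavioural carry and borrow effects, so δ = 0.5 throughout may be too low for some terms. The t-test proxy also does not carry over cleanly to regressions over items.

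A reader might set the roughly 20% of wrong H0 crossings against the quoted 5% and call the 5% false. These are different quantities: one is a first crossing at any look, the other is conditional on reaching the maximum. Under the all-effects rule one crossing stops nothing. If the study runs to 60 per group, the wrong BF01 ≥ 6 rate for the age effect, evaluated at that size, is 2.6–3.7% at assumed intra-subject correlations of 0.50–0.43. The first-crossing rate matters only if that model lies behind the published 61% and 80%.

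It is also fair that reaching the maximum is a planned outcome, that Bayes factors are graded at any size, and that no analysis is invalidated. What survives all this is the mismatch between the rule and the figures.

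**Conclusion.** The point holds as a misstatement of design properties. The rule covers 37 effects, while the 61%, 80% and 5% are single-effect figures from an unnamed test. Under the all-effects rule the chance of stopping by 60 per group is about 0% at ρ = 0, 3–5% at ρ = 0.5 and 20–22% at ρ = 0.8, so the study will most likely run to the maximum. This rests on δ = 0.5 for every effect, t-tests as proxies and assumed correlations. Larger true effects raise the values; true nulls change them further, and in the 64-item regressions a null is hard to confirm at BF01 ≥ 6. The count and the absence of any joint property rest on the text alone.

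**What to change.** Name the test that was simulated and label the three figures as applying to one effect at δ = 0.5. Say whether the 5% is a share of all studies or only of those reaching the maximum.

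Then take one of these routes:
- re-run the design analysis on the planned ANOVA and regression effects under the all-effects rule, and report the joint stopping probability and the misleading-evidence rates in both directions;
- state that 60 per group is the expected sample size;
- prespecify a smaller stopping set, chosen by the authors, with its own simulated properties, and report the remaining effects at whatever sample size results.

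The cost is one simulation and revised text, with less favourable stated figures. No extra participants are needed beyond the maximum already planned. The article is a stage I registered report with data collection still to start, so the change can be made beforehand.

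### The stated 80% chance of stopping before n_max does not fit the plan's own 61% at δ = 0.5, and the 5% misleading-evidence figure lacks its denominator, cut-off and effect size

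*Protocol article*

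**What the plan says.** All the figures stand in the protocol article under Bayes factor design analysis. The plan uses "the sequential Bayes factor design with maximal" n. It "will start with a minimum sample size of" 20 per group, continues until BF10 or BF01 of at least 6 "is obtained for all effects of interest", and "will be stopped when a maximum sample size of" 60 per group has been reached.

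Three operating characteristics are then given, attributed to Monte Carlo simulation:

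- For the maximum: "80% of studies with an infinite sequential sampling stop earlier than" n_max. No effect size or test is attached.
- For studies ended by the maximum: "only with a probability of 5% will the study obtain misleading evidence". No effect size or Bayes factor cut-off is attached.
- For power: "This design detects an expected medium effect size of" δ = 0.5 "with a probability of 61% before the" maximum is reached.

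Under Statistical data analysis, the t-test prior is Cauchy with scale 0.707, age-group contrasts are two-sided independent-samples Bayesian t-tests, and moderate evidence begins at a Bayes factor of 3.

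**The concern.** The 80% and the 61% describe one design with one maximum. A gap of 19 percentage points between stopping early and detecting the effect early would have to be filled by studies that stop early for the null. Whether that can happen with this prior, boundary and sample size can be calculated.

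The figures matter because this is a registered report. Readers will use them to judge how likely the study was to end undecided at 60 per group, and how far to trust a result obtained there. If the 80% is read at the expected effect size, the chance of running to the maximum appears to be 20%.

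**Working it through.** **Inputs from the article.** Start 20 and maximum 60 per group; boundary 6; δ = 0.5; Cauchy scale r = 0.707; two-sided independent-samples t-test.

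**Assumptions.** One participant per group is added at each look, since the article gives no step size. Misleading evidence at the maximum means BF10 < 1/3 when δ = 0.5; this borrows the article's moderate-evidence category.

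**Bayes factor.** With n per group, n_e = n/2 and ν = 2n − 2:

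BF10(t) = ∫ (1 + n_e·g)^(−1/2) · [1 + t²/((1 + n_e·g)·ν)]^(−(ν+1)/2) · p(g) dg ÷ [1 + t²/ν]^(−(ν+1)/2),

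where p(g) is inverse-gamma with shape 1/2 and scale r²/2. BF10 = 6 corresponds to |t| = 2.81 at n = 20 and 2.78 at n = 60.

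**Step 1: the 61% reproduces.** In 100,000 simulated sequences at δ = 0.5, 61.2% reach BF10 ≥ 6 by n = 60 (60.3% strictly before 60). The remaining 38.8% run to the maximum.

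**Step 2: the null boundary is out of reach.** BF01 is largest at t = 0. There it is 3.24 at n = 20 and 5.14 at n = 60. It first exceeds 6 at n = 85 (5.99 at n = 84, 6.03 at n = 85). No run can stop for the null by n = 60, so

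P(stop by 60) = P(detect by 60) + P(stop for null by 60) = 61.2% + 0 = 61.2%.

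The zero comes from the formula and carries no simulation error.

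**Step 3: what would give 80%.**

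| Setting (single contrast) | Share stopping by n = 60 |
|---|---|
| δ = 0.5, step 1 | 61% |
| δ = 0.5, steps of 5 or 10 | 56 to 58% |
| δ = 0.5, one-sided | 74% |
| δ = 0.5, r = 1 | 62% |
| δ = 0.5, r = 1.414 | 74% |
| δ = 0.5, boundary 5 / 4 / 3 | 64% / 75% / 92% |
| δ = 0.5, paired test | 89% |
| δ = 0.61 | 80% |
| δ = 0 | 3.5%, all for H1 |

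Under open-ended sampling at δ = 0.5, the 80th percentile of the stopping n is 89 to 92 per group. At δ = 0 it is about 160.

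**Step 4: the 5%.** At δ = 0.5, 4.87% of all sequences end at n = 60 with BF10 < 1/3, which matches the stated 5%. Among sequences that reach n = 60 the share is 4.87/38.83 = 12.5%; a separate run of 40,000 gave 4.99/38.75 = 12.9%. At δ = 0, BF10 > 1 given that n = 60 is reached occurs in about 4%.

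**The case against.** **The 80% names no effect size.** It may come from another δ or another test, so a contradiction is not proved for every reading. This stands as far as it goes: δ of about 0.61 gives 80%. But the article names no such value, and δ = 0.5 is the only effect size it assigns to this design. On that reading the two figures cannot both hold; on any other, the 80% rests on an undisclosed condition. It needs correcting either way.

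**The 5% might be called irreproducible, or said to contradict the 61%.** A reader might infer this, but the documents do not support it. The 5% comes out of the same simulation as the 61%, and the two are compatible. A reader might also conclude that misleading evidence is about 2.5 times as likely as stated. That ratio depends on a cut-off and effect size the article does not give; under δ = 0 with BF10 > 1 as the criterion, the conditional value is about 4%. What remains is a mismatch between the conditional wording and the reading that reproduces the number.

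**A single contrast is not the study.** Sampling stops only when all effects of interest reach the boundary, and these are ANOVA and regression effects on several outcomes. It would be wrong to say that 61% of whole studies stop by 60. The null result also does not carry over to within-subject effects: for a paired test BF01 can reach 7.08 at n = 60. Both points stand and limit the replacement wording.

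**The practical weight is small.** The 61% is printed shortly after the 80%, the article says the maximum was chosen for feasibility, and no test, prior, threshold or enrolment figure depends on the 80%. That is fair, but the 80% is still offered in support of the maximum.

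**Conclusion.** The point holds for the 80% and, as a matter of wording, for the 5%.

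Under the settings that reproduce the 61%, the share of single two-group contrasts stopping by 60 per group is that same 61%. About 39% run to the maximum, roughly double the 20% that the 80% implies. This rests on the two-sided independent-samples t-test with Cauchy 0.707, boundary 6 and δ = 0.5. Steps of 5 or 10 per group lower the share further.

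The study-level chance of an early stop cannot exceed that of its least favourable required effect, so it should be lower than the single-contrast figure. It cannot be quantified from the article, because the correlations among effects and their sizes are not given.

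The 5% is about right as a share of all studies at δ = 0.5 with BF10 < 1/3 at the maximum. Worded as conditional on reaching the maximum, the same definition gives about 13%.

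Nothing here shows that the stopping rule or the maximum sample size is invalid.

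**What to change.** Under Bayes factor design analysis:

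1. Delete the 80% statement, or replace it with: *For a single two-group contrast at δ = 0.5, about 61% of studies stop by n_max and about 39% run to n_max; under δ = 0 about 3.5% stop by n_max, all for H1. The study-level chance of stopping early is lower, because all effects of interest must reach the boundary.* If the 80% was derived for another effect size or test, name it.
2. Reword the 5% sentence to give its denominator, Bayes factor cut-off and effect size. If it was computed as reproduced here: *At δ = 0.5, about 5% of all studies end at n_max with BF10 < 1/3; among studies that reach n_max this is about 13%.*

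Enrolment, stopping rule, priors and analyses stay unchanged. The only cost is that the stated properties look less favourable.
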